### Comparator group

We are not proposing any change of standard care for the CSI group, save that to maintain participant blindness to the intervention the participants will have 55 ml sample blood taken, which will be taken to the sample preparation area. This blood will be discarded in the sample preparation area whilst a sham-centrifuge process is performed in order to maintain participant blinding. The control participants will then receive the CS injection, which contains Depo-medrone (40 mg) mixed with 3 mls of 0.5% bupivacaine local anaesthetic, administered using standard aseptic techniques, but provided in a ‘blinding syringe’ (non-transparent sides).

### Post-injection follow-up

For both treatments, immediately after the injection the participant will receive standard advice and can immediately resume normal daily activities. After 6–8 weeks if no significant medium-term benefit, as defined by usual clinical assessment, is reported, the patient will be referred to secondary care to discuss alternative treatment options as per standard care pathways.

To ensure that the participant’s clinical team know what treatment they have already received as part of the study when they revert back to their standard care, the participant’s medical notes will state their involvement in the SPIRIT trial and that the site research team should be contacted prior to further treatment commencing to establish which intervention the participant originally received.

### Primary outcome

The primary outcome is the feasibility and acceptability which will be assessed by the rate of patient conversion from eligibility for the study to randomisation. Numbers of screened ineligible patients will be noted to ensure recruitment for the main trial is feasible within this patient population. Numbers of screened eligible participants declining versus converted to randomised participants will be noted to ensure that the conversion rate of eligible to randomised participants is accurately estimated.

### Secondary outcomes

Levels of participant retention and data compliance will be measured by loss to follow-up, missing data and withdrawal at the end of the trial will be collected. Data will be collected on outcomes that we plan to collect in the definitive trial. While this feasibility trial is underpowered to detect meaningful differences, an attempt can be made to ensure all the relevant data are able to be collected. Further, the current favoured outcome measure for the full RCT trial, PROMIS [16], can be assessed as an effective primary outcome and used in the power calculations for the definitive trial.

The following clinical scores will be collected; Oxford Shoulder Score (OSS) [17], Pain visual analogue score (VAS), EQ-5D-5L score [18], Work Productivity Impairment Questionnaire (WPAI) [19] and patient/hospital reported resource use including referral rates for shoulder surgery at baseline, 3 months and 6 months. We will gather data on any complications of either intervention at 6 months.

### Data collection

At baseline demographic data, patient function and pain data using the PROMIS physical function, PROMIS Pain interference, Oxford Shoulder Score, VAS and Work Productivity Impairment questionnaires will be collected after the participant has provided consent. Participants will also be asked to complete the EQ-5D-5L health-related quality-of-life questionnaire to indicate their typical health status. All case report forms (CRFs) including screening, consent, randomisation and baseline assessment will be completed online on the REDCap database.

Data collection will be divided into two phases, early and late phase follow-up:*Early*—participants will receive a weekly text/email/phone call (according to participant preference) up to week 8 post-randomisation with a link to a visual analogue scale (VAS) asking them to indicate their level of pain in the previous 24 h and whether during that week if they have taken any painkillers for their injury.*Late*—at 3 and 6 months post-randomisation, participants will be contacted by the Oxford central study office via automated SMS or email from the REDCap database and invited to complete the PROMIS, OSS, EQ-5D-5L, VAS, WPAI, health resource use and complications questionnaires.

Complication data will be collected from patients at 3 and 6 months post-randomisation. Complications will be patient-reported via their 3- and 6-month questionnaires and verified by research nurses at the site. At 6 months post-randomisation the site staff will be asked to complete a medical notes review to ensure all expected complications are recorded.

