Currently, Corticosteroid injections (CSI) remain the mainstay of initial treatment in the majority of cases of shoulder pain presenting to both general practice and secondary care. The efficacy of CSI has been tested in a number of trials and subsequently through systematic review. These have reported differing conclusions, but the consensus view is that any benefits seen are most likely to be short-term and there remains a significant number of patients who go on to have surgical intervention despite CSI. In addition to the lack of strong evidence towards the efficacy of CSI, there have also been theoretical and lab-based deleterious effects of corticosteroids on tendon biology reported. CSI might impair the potential for intrinsic tendon repair mechanisms but it may increase the risk of subsequent tendon tearing.

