### Aims and objectives

There is a recognition that robust evidence must be produced before blood-derived therapies are further introduced into orthopaedic clinical practice [15]. These therapies are freely available in private practice and their use both in the UK and worldwide is increasing. No similar work currently exists to assess the efficacy of APS in treating shoulder pain. Further, to date, no randomised controlled trial (RCT) has investigated a comparison of CSI and APS for shoulder pain. The best means for evaluation of the clinical and cost-effectiveness of APS versus the current standard of care, CSI, would be to undertake a fully-powered multicentre RCT. However, there are uncertainties, specifically regarding recruitment rates and participant retention, that need to be assessed before undertaking a large-scale RCT.

This feasibility study trial aims to:Examine the conversion rate of eligible to randomised participants and total number of participants recruited.Investigate the levels of retention and data compliance at follow-up dates.Assess whether it is possible to collect the appropriate outcome measures (PROMIS Physical Function (upper extremity), PROMIS pain interference questionnaire[16], Oxford Shoulder Score (OSS) [17], Pain visual analogue score (VAS), EQ-5D-5L score [18], Work Productivity Impairment Questionnaire (WPAI) [19] and patient/hospital reported resource use including referral rates for shoulder surgery) at baseline, 3 months and 6 months.Gather data on any complications of either intervention at 6 months.

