### Adverse event reporting

Both APS and CSI are licenced for use in the UK for shoulder injections and will be delivered in the usual manner. We will collect patient-reported adverse events at 8 weeks, 3 months and 6 months.

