### Serious adverse events

All serious adverse events (SAEs) will be reported in an expedited manner. The following has been defined as any untoward medical occurrent that results in death; is life-threatening; requires inpatient hospitalisation or prolongation of existing hospitalisation; results in persistent or significant disability/incapacity; consists of a congenital anomaly or birth defect. Other ‘important medical events’ may also be considered a serious adverse event when, based upon appropriate medical judgement, the event may jeopardise the participant and may require medical or surgical intervention to prevent one of the outcomes listed above.

Foreseeable SAEs and adverse events not defined as serious that are related to the interventions will be recorded by participants or site staff but will not need to be reported immediately. Foreseeable adverse events to be recorded as complications include: septic arthritis; dizziness; nervousness; facial flushing; insomnia; flare-up of pain intensity at the injection site; Injection site skin pigmentation; subcutaneous fat atrophy.

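### The 6-month notes review is scoped to expected complications although the objective is any complication, and tendon tearing, raised in the Background, is not a named foreseeable event (minor)

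*Protocol article*

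**What the plan says.** The objective on harms appears twice and is broad both times. Aims and objectives has "Gather data on any complications of either intervention at 6 months", and Secondary outcomes repeats it: "We will gather data on any complications of either intervention at 6 months".

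The means of collection are spread over three sections of the Methods:

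- Data collection, patient route: "Complications will be patient-reported via their 3- and 6-month questionnaires and verified by research nurses at the site".
- Data collection, site route, at 6 months after randomisation: "the site staff will be asked to complete a medical notes review to ensure all expected complications are recorded".
- Adverse event reporting: "We will collect patient-reported adverse events at 8 weeks, 3 months and 6 months".
- Serious adverse events: serious events go by expedited reporting, apart from foreseeable ones. Foreseeable serious events and "adverse events not defined as serious that are related to the interventions will be recorded by participants or site staff", without immediate reporting. The section then gives examples: "Foreseeable adverse events to be recorded as complications include: septic arthritis; dizziness; nervousness; facial flushing; insomnia; flare-up of pain intensity at the injection site", followed by skin pigmentation at the injection site and subcutaneous fat atrophy. That makes eight items, and tendon tear is not one of them.

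The Background, discussing theoretical and laboratory findings on corticosteroids and tendon biology, says of CSI that "it may increase the risk of subsequent tendon tearing".

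**The concern.** A notes review at the end of follow-up is useful chiefly because it can find what patients did not report. If its stated purpose is limited to expected complications, it is weakest for the events it is best placed to add. The article does not define which complications are expected, so two sites could reasonably review the same notes to different standards.

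Tendon tear shows why this matters. It is a finding in the clinical record, and its symptoms can resemble the shoulder pain the patient already had. A participant blinded to treatment is poorly placed to attribute it to the injection. Participants without benefit at 6–8 weeks are referred to secondary care (Post-injection follow-up), so such a finding may well reach the notes. At stake is whether the feasibility trial shows that a harm mentioned in its own rationale can be captured before the definitive trial is designed.

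**Working it through.** The point is textual, so the check is to set the sections side by side.

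**Step 1. Scope of the objective against scope of each route.**

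| Route (section) | Starts from | Stated scope |
|---|---|---|
| Objective (Aims; Secondary outcomes) | – | any complication |
| 3- and 6-month questionnaires, nurse-verified (Data collection) | patient | not limited to expected events |
| Adverse events at 8 weeks, 3 and 6 months (Adverse event reporting) | patient | not limited to expected events |
| Expedited reporting (Serious adverse events) | any source | events meeting the seriousness definition |
| Non-serious events (Serious adverse events) | patient or site staff | events related to the interventions |
| Resource use, including surgical referral (Secondary outcomes) | patient or hospital | referrals and resource use, not complications as such |
| 6-month notes review (Data collection) | clinical record | expected complications |

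The last row is the only systematic search for complications that begins in the clinical record, and its stated scope is narrower than the objective.

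**Step 2. Follow an unlisted tear through the routes.** Suppose a tear appears in a scan report and the patient does not mention it.

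- The two patient routes do not pick it up. Nurse verification checks what was reported.
- Expedited reporting picks it up only if it meets the seriousness definition, which a tear need not do.
- Staff recording picks it up if staff judge it related. Nothing in the foreseeable list prompts that judgement.
- Resource use may count a surgical referral, but not the tear itself.
- The notes review would see the report, but its stated purpose does not require the tear to be recorded unless the site counts it as expected.

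So the event can be captured, but no route as worded ensures it.

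**Step 3. Does any planned figure move?** Statistical considerations gives 40 participants before loss and 20% loss: 40 / (1 − 0.20) = 50, which matches the stated sample size. The point does not enter this calculation.

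**Step 4. Context for size.** With 1:1 allocation, 50 participants give 25 per arm. The documents give no complication rates, so the rates here are assumptions. The chance of at least one event in an arm is 1 − (1 − p)^25:

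| Assumed rate p | Chance of at least one event in 25 |
|---|---|
| 1% | 22% |
| 2% | 40% |
| 5% | 72% |
| 10% | 93% |

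With zero events in 25, the one-sided 95% upper bound on the rate is 1 − 0.05^(1/25) = 11.3%. Even with complete capture, the trial would say little about the rate of an uncommon harm. What it can show is whether the capture process works.

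**The case against.** The strongest reply is that the sentence on the notes review sets a minimum. It says what the review must secure and does not tell staff to ignore anything else. The list of foreseeable events is introduced as a set of examples, and Data collection does not tie its notion of expected complications to that list. This stands. A reader might infer that the review is confined to the eight items, or that a site finding a tear has no basis for recording it. The text supports neither: staff may record any non-serious event they judge related, listed or not.

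A second reply is that other routes exist. This also stands, so it would be wrong to say that unlisted events rest on self-report alone.

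A third is that the tendon-tear concern is introduced as theoretical and laboratory-based. That is correct, and it limits the weight the omission can bear. It does not explain why a harm thought worth raising in the rationale is not a named item.

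A fourth is that the article condenses a fuller protocol, and that the review form may be broader. That may be so. But the article does state a scope for the review, and the scope it states differs from the objective it states.

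**Conclusion.** The point holds as a minor mismatch. The stated purpose of the notes review is narrower than the stated objective, and the list of named events does not match the Background. The objective is not defeated. The exposure is limited to unexpected complications that the patient does not report, or that staff do not judge related. This assumes that sites follow the review sentence as written and do not treat it as a floor.

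Three stronger readings are not supported:

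- *That up to 20% of unlisted events would be lost.* The 20% is a sample-size allowance for loss to follow-up. It does not count people with no report at any time: someone lost by 6 months may have answered at 8 weeks or 3 months, and the staff and serious-event routes remain. The documents allow no estimate of the proportion missed.
- *That complications of autologous protein solution (APS) are likely to be unexpected because it has never been used in the shoulder.* Aims and objectives speaks of missing efficacy work and of no randomised comparison with CSI. It also describes growing use of blood-derived therapies, and Adverse event reporting describes both treatments as licensed for shoulder injection.
- *That capture would differ between arms.* The same review applies to both. A difference is possible if the kinds of event differ by arm, but nothing in the documents shows it.

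Complications are a descriptive secondary item in a trial of 50. The primary outcome, the progression criterion and the sample size are unaffected.

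**What to change.** 1. In Data collection, state that the 6-month notes review records all complications found in the notes, expected or not, by the same procedure in both arms.
2. Reconcile the foreseeable-event list under Serious adverse events with the Background by naming, as a recorded item, any rotator cuff tear documented in existing records after the injection. Do not label it new or progressed: the article describes no baseline imaging, and a pre-existing tear is not a listed exclusion, so the notes could not reliably separate the two.

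The cost is a slightly longer review of notes that are already to be read, and some recorded tears that may predate the injection. The report should say so when it presents them. No scans, visits or participants are added.

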### Adverse event reporting

Both APS and CSI are licenced for use in the UK for shoulder injections and will be delivered in the usual manner. We will collect patient-reported adverse events at 8 weeks, 3 months and 6 months.

### Serious adverse events

All serious adverse events (SAEs) will be reported in an expedited manner. The following has been defined as any untoward medical occurrent that results in death; is life-threatening; requires inpatient hospitalisation or prolongation of existing hospitalisation; results in persistent or significant disability/incapacity; consists of a congenital anomaly or birth defect. Other ‘important medical events’ may also be considered a serious adverse event when, based upon appropriate medical judgement, the event may jeopardise the participant and may require medical or surgical intervention to prevent one of the outcomes listed above.

Foreseeable SAEs and adverse events not defined as serious that are related to the interventions will be recorded by participants or site staff but will not need to be reported immediately. Foreseeable adverse events to be recorded as complications include: septic arthritis; dizziness; nervousness; facial flushing; insomnia; flare-up of pain intensity at the injection site; Injection site skin pigmentation; subcutaneous fat atrophy.

### Statistical considerations and data analysis

Fifty participants will be recruited for this feasibility study. This sample size will be sufficient to estimate the rate of recruitment (i.e., participants randomised out of those screened) and retention.

Fifty participants should provide a robust estimate of the standard deviation around the PROMIS upper limb physical function to be used in the sample size calculation for a definitive trial. Specifically, to prepare for a definitive trial with an anticipated small standardised difference (0.1–0.3) and 80% power, a pilot study sample size of 40 participants (20 per arm) would be sufficient to estimate reliable input parameters for the sample size estimation of the definitive trial [20]; 50 participants will allow for up to 20% loss to follow-up.

The data analysis will be mainly descriptive for the feasibility trial, focussing on the primary outcome, i.e. the conversion rate of eligible to randomised participants, and the total number of participants recruited, as well as on retention and compliance data. Data on patient-reported outcomes, adverse events and complications will also be presented.

Descriptive statistics will be presented for all patient-reported outcomes at baseline and follow-up. Complications and adverse events/serious adverse events reported during the trial follow-up will also be summarised. Data will be presented by the treatment arm and overall. Mean and standard deviation (or median and interquartile range if non-normally distributed) for continuous variables and the number and percentage of participants in each group for binary or categorical variables will be presented.

Differences in outcomes between treatment arms at the follow-up time points will be presented as mean differences with corresponding 90% confidence intervals for continuous data, and risk differences and odds ratios with 90% confidence intervals for binary data, where appropriate. If sufficient outcome data are available, differences will be adjusted for the duration of symptoms (< = / > 6 months) and baseline scores for continuous variables, where applicable, and derived from multilevel mixed-effects linear or logistic regression models. If insufficient data are available, unadjusted differences will be presented.

Summaries by treatment arm will be based on the intention to treat (ITT) population. The ITT population will include all participants with available data for at least one of the follow-up timepoints up to and including 6 months follow-up in the randomised groups to which they were allocated regardless of the treatment they received.

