## Methods

### Trial design and setting

This is a feasibility study of a participant-blinded, parallel group randomised controlled trial. Participants will be followed up clinically as per NHS standard of care. They will also be followed up via questionnaires by the central trial team for a period of 6 months post-treatment. We will recruit 50 participants from two NHS Musculoskeletal (MSK)–triage centres, one in Oxford and the other in Leeds from an existing standard treatment pathway (Fig. 1). The trial will be conducted in accordance with the UK Policy Framework for Health and Social Care Research, the applicable UK Statutory Instruments, (which include the Data Protection Act 2018) and the principles of Good Clinical Practice. The study is following protocol version 1.0 (30 July 2021), Oxford University, Oxford, England, is the sponsor for this trial. The study is funded by the National Institute for Health Research–Research for Patient Benefit, NIHR 201473, Trial Registration Number (please complete).

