### Randomisation and blinding

Once informed consent has been obtained, eligibility confirmed and baseline data collected, participants will be randomised at the level of the individual on a 1:1 basis to either a Corticosteroid injection or an Autologous Protein Solution injection. Randomisation will be performed via a secure web-based service provided by the Oxford Clinical Trials Unit. Randomisation will be stratified by centre, duration of symptoms (≤ / > 6 months) and baseline PROMIS pain interference scores.

To avoid bias in the delivery of the intervention and completion of participants’ reported outcomes, the participants are to be kept blind about the treatment that is allocated. This blinding will be achieved by collecting the blood sample required for APS (55 ml), from both groups of patients. In the intervention group, this blood will be used for the preparation of the APS; in the control group, this blood will be sham prepared as APS, but discarded. The injections will then be performed using opaque syringes to prevent unblinding the patient.

Both the APS and the comparator group will undergo structural physiotherapy, the timing of which will begin either before or after the injection has taken place, as per local protocols. Both injections, where possible, will be undertaken under ultrasound guidance.

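### The adjusted analysis does not carry over all three stratification factors: baseline pain interference is left out for every outcome but itself, and centre is not a listed covariate

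*Protocol article*

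**What the plan says.** Protocol article, Randomisation and blinding: allocation is individual and 1:1, and "Randomisation will be stratified by centre, duration of symptoms (≤ / > 6 months) and baseline PROMIS pain interference scores". That makes three stratification factors.

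Protocol article, Statistical considerations and data analysis: "If sufficient outcome data are available, differences will be adjusted for the duration of symptoms" and for "baseline scores for continuous variables, where applicable, and derived from multilevel mixed-effects linear or logistic regression models". The differences carry 90% confidence intervals. The section adds a fallback: "If insufficient data are available, unadjusted differences will be presented". It does not name the level of the multilevel model.

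Protocol article, Trial design and setting: "We will recruit 50 participants from two NHS Musculoskeletal (MSK)–triage centres, one in Oxford and the other in Leeds". Under Data collection, the outcome questionnaires are repeated at 3 and 6 months, so either centre or participant could be the grouping level.

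**The concern.** Stratifying on a prognostic factor balances it between arms and so removes part of the chance variation in the treatment difference. An analysis that leaves the factor out does not credit that gain: its standard error still counts the variation that the design has removed. The interval is then wider than it need be and covers more often than its nominal level.

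Only one of the three factors, symptom duration, is a named covariate for every outcome. The article fixes this list itself, and it does not match the article's own randomisation scheme, so the point is more than a detail left to the statistical analysis plan. At stake is the precision of the between-arm differences and the model that the definitive trial may inherit.

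**Working it through.** **1. Design factors against model terms**

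| Stratification factor | In the adjusted analysis? |
|---|---|
| Symptom duration (≤ / > 6 months) | Yes, for all adjusted outcomes |
| Baseline PROMIS pain interference | Only as the own-baseline score when pain interference is the outcome; not for PROMIS physical function, OSS, VAS, EQ-5D-5L, WPAI or binary outcomes |
| Centre (two) | Not listed; possibly the unnamed level of the mixed model |

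**2. Number analysed.** The article takes 40 evaluable participants and allows 20% loss: 40 / (1 − 0.20) = 50. This reproduces its sample size, so 40 is used below.

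**3. Effect on the intervals.** Two simulations were run, each with 4,000 trials per scenario, eight strata (2 × 2 × 2) and blocks of 4. The block size, the two-way split of pain interference and all prognostic effects are assumptions; the article gives none of them. Centre is not modelled under the planned covariates.

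*Simulation A*: pain-interference coefficient 0.2–0.35 per SD, centre effect 0–0.5, outcome SD about 1.05. The ratio of 90% interval widths, planned covariates to all stratifiers, was 1.01, 1.04 and 1.10. Coverage was 0.902–0.923 with the planned covariates and 0.898–0.909 with all stratifiers.

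*Simulation B*: residual SD 1, no treatment effect, 40 of 50 analysed, ordinary least squares, own baseline 0.5 per SD.

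| Assumed effects (centre; duration; pain interference per SD) | Covariates | Mean 90% width | Coverage | Empirical SE |
|---|---|---|---|---|
| 0.3; 0.3; 0.3 | duration + own baseline | 1.129 | 0.905 | 0.332 |
| | + centre + pain interference | 1.099 | 0.900 | 0.329 |
| 0.8; 0.5; 0.5 | duration + own baseline | 1.259 | 0.916 | 0.353 |
| | + centre + pain interference | 1.099 | 0.899 | 0.329 |

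Width ratios: 1.129 / 1.099 = 1.03 and 1.259 / 1.099 = 1.15. Across both simulations the excess width is therefore about 1–15%.

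The Monte Carlo error of a coverage figure near 0.90 is √(0.90 × 0.10 / 4000) = 0.005. The 0.905 is thus barely distinguishable from nominal. The 0.916 is clearly above it, by (0.916 − 0.900) / 0.005 ≈ 3 standard errors.

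**4. If centre is the random level.** With two centres of 20, simulation B's variance estimator gave zero in 63%, 52% and 42% of datasets at assumed intraclass correlations of 0.01, 0.05 and 0.10. Separately, 300 REML fits per scenario under simulation A gave a zero or failed variance in 61%, 37% and 17% at centre effects of 0, 0.3 and 0.5. A zero estimate leaves centre out of the fitted model.

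**5. Degrees of freedom.** Intercept, arm, duration and own baseline leave 40 − 4 = 36. Adding centre and pain interference leaves 40 − 6 = 34.

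**The case against.** The strongest reply is that nothing decisive rests on these intervals. The primary outcome is conversion from eligible to randomised, progression depends on recruiting 50 patients, and the article calls the trial underpowered for meaningful differences and its analysis mainly descriptive. The error is also on the conservative side. All of this stands and limits the weight of the point.

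A second reply is that baseline scores might be meant to include the pain interference score used for stratification. The text ties them to continuous variables, so the natural reading is each outcome's own baseline. If the other reading is intended, the wording needs to say so.

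Four stronger readings are tempting, and the documents do not support them.

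- *Centre is omitted and a two-centre random effect is also misused.* These are alternatives. If centre is the level, it is not omitted; if participant is the level, the two-centre objection falls away. A zero variance estimate is also commonest when the true centre effect is nil, where losing centre does little harm.
- *The fallback to unadjusted differences lets the analyst choose after seeing results.* The trigger is the amount of outcome data, not the observed treatment effect. A fallback is ordinary practice when a logistic model cannot be supported, and its threshold can properly sit in a statistical analysis plan.
- *An inflated residual SD will pass to the definitive trial.* The article says only that the SD of PROMIS physical function will be estimated. It does not say that the SD comes from this regression, and a descriptive SD does not depend on the covariates.
- *The intervals are invalid.* In both simulations the planned covariates gave coverage at or slightly above 90%.

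**Conclusion.** The mismatch between the stratification factors and the covariate list is in the text. For pain interference it holds whichever level the mixed model uses; for centre it is conditional on that level. The consequence is a modest loss of precision: 90% intervals about 1–15% wider than with all stratifiers, and coverage of roughly 90–92%. The upper end needs strong effects (centre 0.8, pain interference 0.5 per SD, in residual-SD units). These figures rest on assumed effects, blocks of 4, eight strata, 40 analysed and centre not modelled. Validity is not threatened, and no feasibility conclusion or progression decision changes. It is worth correcting because the correction costs almost nothing.

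**What to change.** In Statistical considerations and data analysis, state one model for continuous outcomes: arm, centre as a fixed effect, symptom duration, baseline PROMIS pain interference as a continuous covariate, and the outcome's own baseline. For pain interference the last two coincide. Use a participant random effect only if 3 and 6 months are modelled jointly, and name that level. A fixed centre effect settles both readings of the present text.

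The cost is a change of wording and about two degrees of freedom (36 to 34 with 40 analysed). No new data are needed: the two added covariates must already be known at randomisation.
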